### 2.13. Compliance with Trial Treatment

Compliance to visit the dental clinic at designated intervals will be conducted by text messages/telephonic reminders to parents. If the child misses an appointment or wants a reschedule, then it is rescheduled with a plus or minus of three days. If the child misses two rescheduled appointment, then it is referred to as non-compliant and the child is withdrawn from the study. However, if the child completes six months (1st outcome assessment) and then becomes non-compliant, the person-time of the participation in the trial will be calculated and will be used for analysis.

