### 2.11. Sample Size

The sample size was calculated based on the primary objective. In an exploration study [26], those children treated weekly with 38% SDF had a slightly higher proportion of arrested caries compared to annual application. There was no considerable difference in the proportion of caries arresting by either semiannual or annual application (less than 10%). We expect that the proportion of the arrested carious lesion not to be more than 14% between the two frequencies of application. Considering a slightly higher proportion of caries arrest by the four times application as compared to others, we estimated the sample size at the power of 0.80 and alpha error of 0.05 to be 120 per arm. Being a population (tribal), which is not mainstream and owing to the demands of multiple follows of the tribal population, it is expected that we could encounter a lost-to-follow-up of about 30%. Accordingly, the final sample size has been increased to 160 children per arm. In total, 480 children will be enrolled on the trial.

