The study requirements, ensuring standardization in the assessment of the cavitated dental lesion, assessment of arrested lesion, application of the 38% SDF varnish to the child, counselling for adherence and eliciting of information from study participants in a uniform reproducible manner will be undertaken before the beginning of the trial at Amrita Kripa Health Care Centre. The data to be collected and the procedures to be conducted at each visit will be reinforced to all the personnel related to the trial. Entering data forms, responding to data discrepancy queries and general information about obtaining research quality data will also be covered during the training session. Calibration will be performed before and during the trial, and reliability expressed using Cohen’s kappa statistic. Once a child is enrolled or randomized, the study site (Amrita Kripa Health Care Centre) will make every reasonable effort to follow the child for the entire study period of 12 months.

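### The three-day rescheduling rule also governs the assessment-only 12-month visit, so an obtainable late outcome goes uncollected and is replaced by person-time or imputation

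*Protocol article*

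**What the plan says.** Section 2.13 opens with reminders for all clinic visits: "Compliance to visit the dental clinic at designated intervals will be conducted by text messages/telephonic reminders to parents". It then sets one rescheduling rule: when a child misses an appointment or asks to move it, "it is rescheduled with a plus or minus of three days". The consequence of repeated absence follows: "If the child misses two rescheduled appointment, then it is referred to as non-compliant and the child is withdrawn from the study". A separate provision covers later non-compliance: "if the child completes six months (1st outcome assessment) and then becomes non-compliant, the person-time of the participation in the trial will be calculated", and that person-time then enters the analysis.

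Section 5 adds that children who drop out after six months stay in the analysis, with missing values imputed.

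Section 2.12 says that, once a child is enrolled or randomised, the site "will make every reasonable effort to follow the child for the entire study period of 12 months".

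Table 1 lists the 12-month visit as oral examination, outcome assessment and adverse event assessment. SDF application is marked No for all three groups at that visit. Section 2.8 places the outcome assessment at 6 and 12 months in every arm.

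**The concern.** A window of a few days may be reasonable where visits are two weeks apart. The same window is applied to an examination one year after baseline at which nothing is administered. A family that can return only a few weeks late would miss the rescheduled dates and be classed as non-compliant, and no provision accepts the late examination. An outcome that the blinded assessors could have recorded is then not recorded.

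The protocol itself anticipates difficulty in keeping these families: "it is expected that we could encounter a lost-to-follow-up of about 30" per cent (Section 2.11). If late attenders differ from punctual ones, which is plausible but not shown in the documents, the missing 12-month outcomes would be selective. There may also be a knock-on effect. Section 5 uses attrition of 15% to choose between per-protocol and intention-to-treat analysis. If children made non-compliant by this rule count as attrition, which the article does not state, the visit window would bear on that choice too.

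**Working it through.** The plan gives no figure on this point to reproduce. The check is a reading of the sections against one another, with a little arithmetic.

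**1. Does the rule reach month 12?** The heading of Section 2.13 refers to treatment, so one could read the rule as limited to application visits. Its last provision rules that out. It deals with the case "if the child completes six months (1st outcome assessment) and then becomes non-compliant". Table 1 has six visits: baseline, 2, 4 and 8 weeks, 6 months and 12 months. After the 6-month visit only month 12 remains in any arm, so the provision has no application unless missing month 12 counts as non-compliance.

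**2. Is month 12 assessment-only?** Applications by arm (Section 2.7 and Table 1):

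| Arm | Applications | At 12 months |
|---|---|---|
| 1 | baseline | none |
| 2 | baseline, 6 months | none |
| 3 | baseline, weeks 2, 4 and 8 | none |

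**3. How late may a child be?** As a share of a 365-day follow-up:
- one shift of three days: 3/365 = 0.8%
- two successive shifts, on the most generous reading: 6/365 = 1.6%
- three weeks late: 21/365 = 5.8%
- four weeks late: 28/365 = 7.7%

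Even two successive shifts do not reach a child who is three weeks late. The text does not say whether the second reschedule is counted from the original date or from the first rescheduled date.

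**4. What takes the place of the observation?** Section 2.13 gives person-time. Section 4 defines a binary outcome, compares proportions by chi-square and regresses a percentage per child; none of these uses person-time. Section 5 gives imputation, which fills in a value that could have been observed.

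**5. Can the retained 6-month result stand in?** Number of applications given before each assessment:

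| Arm | Before month 6 | Before month 12 |
|---|---|---|
| 1 | 1 | 1 |
| 2 | 1 | 2 |
| 3 | 4 | 4 |

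Arm 2 has its second application at the 6-month visit itself. Up to that assessment arms 1 and 2 have been treated alike, so only month 12 can show a difference between annual and bi-annual application, a contrast named in the primary objective.

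**6. How large is the effect?** If a share x of children could be examined only outside the window, 160 × x 12-month outcomes per arm would go uncollected. The documents give neither x nor anything from which to derive it. The effect on power cannot be computed.

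**The case against.** The strongest reply is that the plan already protects these children. Non-compliance needs two missed rescheduled appointments, not one late arrival. The 6-month primary assessment is kept, and Section 5 keeps later dropouts in the analysis with imputation. All of this stands. A reader might infer that a late child is written off as missing on the primary endpoint; the documents do not support that. What is lost is the 12-month observation, not the child.

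A second reply is that no sentence says a late examination would be refused, that Section 2.13 describes rebooking and not an analysis window, and that an article may leave such windows to a fuller document. This is partly right: the rejection follows from applying the rule as written. But the rule is stated, it exempts no visit, and it attaches a consequence at month 12, so this is more than an omitted detail.

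A third reply is that reminders and two reschedules are already a reasonable effort under Section 2.12. That is fair, so the two sections are better described as in tension than in contradiction.

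A fourth reply is that a wider window is not neutral. From last application to month 12 is about 52, 26 and 44 weeks in arms 1, 2 and 3 (52 − 0, 52 − 26, 52 − 8). Four extra weeks would add 4/52 = 7.7%, 4/26 = 15.4% and 4/44 = 9.1%. Section 2.8 also counts exfoliated treated teeth as arrested, so longer observation can add arrests. This stands as a reason to fix the window in advance, keep it identical in all arms, record dates and run a sensitivity analysis.

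Finally, a reader might infer that a wider window would recover part of the expected 30% loss, for example raising observed children from 160 × 0.70 = 112 to 160 × 0.75 = 120 per arm. Section 2.11 attributes that loss to the population and the number of follow-ups, not to the window, and nothing shows how much of it is recoverable.

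**Conclusion.** The point holds in a limited form. As written, the three-day rule governs an examination at which no treatment is given. Followed literally, it leaves an obtainable 12-month outcome uncollected and puts person-time or an imputed value in its place. That is hard to square with the commitment to follow every child for 12 months, and it falls on the only time point that can separate annual from bi-annual application.

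The conclusion rests on two readings: that Section 2.13 applies to every scheduled visit, which its own provision on later non-compliance requires, and that a child classed as non-compliant is not examined afterwards, since no section provides for it. The number of children affected is unknown, so no loss of sample size or power is claimed. The change is worth making because it is cheap and keeps real data.

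**What to change.** In Section 2.13, separate the window for outcome assessment from the window for treatment visits. For the 12-month examination:
- set a wider pre-specified window of the sponsor's choosing, identical in all arms, and keep trying to obtain the examination until it closes;
- record the actual date and analyse the examination as the 12-month outcome;
- add a sensitivity analysis limited to examinations near the nominal date.

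Align Section 2.10 (one year of participation), Section 2.12 (follow-up commitment), Section 3 (end of trial at 12 months from baseline) and Section 5 (handling of dropouts) with the new window, so that they agree on whether a late examination is accepted and how the child is then analysed. The timing of treatment visits is a matter for the clinical team and is not part of this request.

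The cost is a short amendment across these sections, some extra scheduling at one site, a possibly later end of trial, and somewhat more variable follow-up time, which the recorded dates and the sensitivity analysis address.

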### 2.10. Participation Timeline

Each eligible child will be a part of the trial for one year from their baseline visit. The total number of visits depends on the study arms to which child is allocated (Figure 1).

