## 4. Statistical Methods

The outcome of the treated carious lesion is binary, either arrested lesion or failed to arrest at 6 months follow-up and at the end of 12 months follow up visit. The outcome will be assessed at two levels: Tooth-level—the proportion of cavitated surfaces at baseline will be compared with the proportion of the surfaces arrested at each frequency of application at 6 months follow-up and the end 12 months using chi-square methods. Between three frequencies of application (annual, semi-annual, and four times a year applications) the proportion of arrested surface at 6 months follow-up and end 12 months will be compared. This comparison will be stratified by type of tooth (posterior vs. anterior) and type of surfaces (facials vs. lingual). Child-level—each child may have one or more cavitated carious surface treated with SDF. So, the per-child proportion of cavitated carious lesions at baseline treated with 38% SDF applied at different frequencies that stayed arrested throughout observation will be determined.

The regression will be modelled on the dependent variable as a percentage of the arrested carious lesion per child with another. The two sets of analysis will be done, first, the intention-to-treat set, considering all patients as randomized regardless of whether they received the randomized treatment, and second, the “per protocol” analysis set. The hypothesis that four times application of 38% of SDF superior to other frequencies (annual or semi-annual application) is accepted, only if shown to be superior using both the “intention to treat” and “per protocol” analysis sets.

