## 5. Analysis Population and Missing Data

The reasons for withdrawal in each group will be assessed and reported qualitatively. The effect that any missing data might have on results will be assessed via sensitivity analysis of augmented data sets. Dropouts (after six months) will be included in the analysis and values will be imputed for missing data. If the attrition loss is less than 15%, “per protocol analysis” will be carried out otherwise “Intention to treat” will be performed.

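### Children withdrawn for missed visits before 6 months appear to have no outcome sought and no place in the analysis, which conflicts with the stated intention-to-treat set and may affect the arms unequally

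*Protocol article*

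**What the plan says.** All references are to the protocol article.

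- **Section 2.13 (compliance).** A missed visit may be moved within a narrow window: "it is rescheduled with a plus or minus of three days". After that, "If the child misses two rescheduled appointment, then it is referred to as non-compliant and the child is withdrawn from the study". One exception follows: "if the child completes six months (1st outcome assessment) and then becomes non-compliant, the person-time of the participation in the trial will be calculated".
- **Section 5 (missing data).** "Dropouts (after six months) will be included in the analysis and values will be imputed for missing data". The section also plans a sensitivity analysis on augmented data sets, without saying which children those contain.
- **Section 4 (statistical methods).** ITT is defined as "considering all patients as randomized regardless of whether they received the randomized treatment". Superiority of four applications is accepted "only if shown to be superior using both the “intention to treat” and “per protocol” analysis sets".
- **Section 2.12 (implementation).** The site commits to reasonable efforts to follow each enrolled or randomised child for the full 12 months.
- **Sections 2.7 and 2.10, Table 1 (visits).** Arm 3 has applications at baseline and weeks 2, 4 and 8; arm 1 at baseline only; arm 2 at baseline and 6 months. Section 2.10 adds: "The total number of visits depends on the study arms to which child is allocated". Table 1 splits the application rows by arm, but marks oral examination and adverse-event assessment at weeks 2, 4 and 8 without any split.

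**The concern.** The rule ends participation in the study, not just adherence to the schedule. A child who misses visits early is therefore not assessed at 6 or 12 months. ITT exists to keep such children in the comparison. If they are gone, the ITT set moves towards the per-protocol set, and requiring superiority in both protects less than it appears to.

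The loss may also be uneven. If only arm 3 attends at weeks 2, 4 and 8, a child there has four post-baseline occasions to fail by 6 months, against one in arms 1 and 2. Arm 3 would then keep a more adherent group of families. An analysis plan written later can impute for these children but cannot recover outcomes that were never sought.

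A smaller inconsistency sits alongside. For non-compliance after 6 months, Section 2.13 says "the person-time of the participation in the trial will be calculated and will be used for analysis", while Section 5 imputes for drop-outs over the same period and Section 4 analyses a binary outcome at fixed visits.

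**Working it through.** **Text against text.** The plan gives no figure to reproduce here, so the first check is what each section does with a child who becomes non-compliant at, say, week 8.

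| Section | Treatment of that child |
|---|---|
| 2.12 | Followed for 12 months as far as reasonable |
| 2.13 | Withdrawn; the exception requires a completed 6-month assessment, so it does not apply |
| 5 | Not among the drop-outs named for inclusion and imputation |
| 4 | Belongs to ITT as randomised |

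Sections 2.12 and 4 keep the child; Sections 2.13 and 5 do not.

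**Illustration of a between-arm effect.** Nothing in the documents gives attendance by arm or arrest by adherence, so these inputs are assumed: a low-adherence group of 20% with 50% arrest, 75% arrest in the other 80%, no effect of application frequency, and failures only in the low-adherence group. True arrest in every arm is 0.20 × 0.50 + 0.80 × 0.75 = 70.0%. From the documents: 160 children per arm and a 14-point planning difference (Section 2.11). Visits due up to and including 6 months are one in arms 1 and 2 and four in arm 3, if weeks 2, 4 and 8 apply to arm 3 only.

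With per-visit failure risk g inside the low-adherence group and k visits, the share of that group remaining is r = (1 − g)^k. Observed arrest is (0.20 × r × 0.50 + 0.80 × 0.75) / (0.20 × r + 0.80).

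*5% overall failure at the first visit*, so g = 0.05/0.20 = 0.25:
- Arms 1 and 2: r = 0.75. Withdrawn 0.20 × 0.25 = 5.0% (8 of 160). Arrest (0.075 + 0.600)/0.950 = 71.1%.
- Arm 3: r = 0.75^4 = 0.3164. Withdrawn 0.20 × 0.6836 = 13.7% (about 22 of 160). Arrest (0.0316 + 0.600)/0.8633 = 73.2%.
- Gap 2.1 points; 2.1/14 = 15% of the planning difference.

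*3% overall failure at the first visit*, so g = 0.03/0.20 = 0.15:
- Arms 1 and 2: r = 0.85. Arrest (0.085 + 0.600)/0.970 = 70.6%.
- Arm 3: r = 0.85^4 = 0.5220. Withdrawn 9.6% (about 15 of 160). Arrest (0.0522 + 0.600)/0.9044 = 72.1%.
- Gap 1.5 points; 1.5/14 = 11%.

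**Two other readings.**
- *The two missed rescheduled appointments belong to two different visits.* Arms 1 and 2 cannot trigger the rule by 6 months and stay at 70.0%. In arm 3 the share of the low-adherence group remaining is r = (1 − g)^4 + 4g(1 − g)^3. At g = 0.25, r = 0.3164 + 0.4219 = 0.7383, arrest (0.0738 + 0.600)/0.9477 = 71.1%, gap 1.1 points. At g = 0.15, r = 0.5220 + 0.3685 = 0.8905, arrest (0.0890 + 0.600)/0.9781 = 70.4%, gap 0.4 points.
- *All arms attend weeks 2, 4 and 8.* The loss is the same in each arm and the gap is zero. At g = 0.25 every arm would show 73.2% against a true 70.0%, so the arrest rate is still overstated and ITT is still incomplete.

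**The case against.** **Exclusion is never stated outright.** This is correct: it follows from the exception in Section 2.13 and the six-month limit in Section 5. But both sections carry the same limit and no other text gives these children an outcome or an imputation. It also concerns drop-outs only; a reader might infer that completers are left out, and nothing says so.

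**Other text softens the rule.** The follow-up commitment in Section 2.12 and the sensitivity analysis in Section 5 both bear on the point. The first contradicts the withdrawal rule and does not override it. The second is not said to bring early withdrawals back.

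**The imbalance is inferred.** This stands. Sections 2.7 and 2.10 point to arm-specific visits, but Table 1 can be read as all arms attending at weeks 2, 4 and 8, and the flow diagram that Section 2.10 refers to is not available here. A reader might take a loss concentrated in arm 3 as established; the documents do not settle it.

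**The direction is assumed.** This also stands. Bias favours arm 3 only if non-attenders have worse arrest, which is plausible but undocumented.

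**The size could be overstated.** A reader might apply 1 − 0.95^4 = 18.5% loss to arm 3 and draw all of it from the 20% low-adherence group, giving 74.5% against 71.1%, about 3.5 points. That mixes a risk shared by all children with withdrawals from one group only, and empties 93% of that group. Keeping the risk inside the group throughout gives 2.1 points.

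**Person-time is not foreign to the plan.** Section 2.8 censors by duration of participation when teeth are restored, and the child-level outcome in Section 4 refers to lesions staying arrested over observation. So the sentence needs reconciling, and the text does not support simply striking it out.

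**Conclusion.** The conflict is real and rests on the protocol's own text. Early withdrawals are, by implication, neither assessed nor imputed, although ITT is defined on all children as randomised and 12-month follow-up is promised. It should be corrected in the protocol, because it determines which outcomes are collected.

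A differential effect between arms is conditional. It requires that weeks 2, 4 and 8 apply to arm 3 only and that non-attenders have worse arrest. Under the assumed values the spurious gap in favour of arm 3 is about 2.1 points at 5% first-visit failure and 1.5 at 3%. It is about 1.1 and 0.4 if two different visits must be missed, and zero if all arms attend. These figures show a scale against the 14-point planning difference and are not estimates for this trial. The conflict over ITT remains under every one of these readings.

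**What to change.** 1. In Section 2.13, replace withdrawal from the study with wording such as: 'recorded as non-compliant; the scheduled 6- and 12-month outcome assessments are still sought unless consent is withdrawn'. This concerns follow-up only and takes no position on further applications.
2. In Sections 4 and 5, state that ITT includes every randomised child, with multiple imputation of missing 6- and 12-month outcomes whenever the loss occurred. Use non-compliance only to define the per-protocol set.
3. Reconcile the person-time sentence in Section 2.13 with imputation in Section 5, the fixed-visit binary analysis in Section 4 and censoring in Section 2.8.
4. Reconcile Table 1 with Sections 2.7 and 2.10 on which arms attend at weeks 2, 4 and 8, and say whether the two missed rescheduled appointments belong to one visit or two.

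**Cost.** The 6- and 12-month assessments are already scheduled for all arms, so no new procedure is needed. Families who missed visits did so despite the text and telephone reminders in Section 2.13, so reaching them will take some extra contact effort. Some outcomes will still be missing, and for those the result will depend on the imputation.

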### 2.14. Adverse Events

The 38% SDF used in this trial is employed in routine clinical practice as a standard of care procedure. The potential risks for a child are minimal and identical to the risk for children obtaining routine dental care. The only foreseeable risk would be an allergic reaction to SDF. Silver diamine fluoride stains clinic surfaces and clothes. At each contact with the study participant, investigators will seek information on adverse events by specific questions and an oral examination.

The child may experience a transient metallic or bitter taste. Even a small amount of silver diammine fluoride can cause a “temporary tattoo” to the skin (on the patient or dentist). The patient will be informed about the same during the consenting process and reinforced during the follow-up visits. If the child/parent refuses to participate at any point in time owing to any of the above-mentioned conditions, he/she will be considered as a drop-out. Stain on the skin resolves with the natural exfoliation of the skin, usually in 2–14 days. Universal precautions will prevent most exposures to the adjacent tissues. Isolation of the areas to be treated with cotton rolls and application cocoa butter to protect surrounding gingival tissues will prevent inadvertent exposure. Spills can be cleaned up immediately with copious water, ethanol, or bleach. High pH solvents such as ammonia may also be used. Secondary containers and plastic liners for surfaces are adequate preventives.

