### 2.7. Interventions

#### Silver Diammine Fluoride

SDF is a colorless liquid containing silver ionic particles. It contains 38% (44,800 ppm) fluoride ion at a pH of 10. This formulation constitutes 25% silver, 8% ammonia, 5% fluoride, and 62% water. One drop (0.05 mL) of 38% SDF solution (2.24 F-ion mg/dose) is required for the treatment of one tooth. The SDF treatment protocol consists of removing gross debris from the cavitated tooth, drying the affected area, isolating the tooth with the help of cotton rolls and suction, placing a small amount of SDF on the affected area, gently drying the SDF for 1 min, removing excess SDF with cotton gauze and isolating the tooth for up to 3 min [34]. This procedure will be performed after the tooth is removed of debris (with the aid of a toothbrush) and soft caries using a spoon excavator. It includes gross debris from cavitation to allow better SDF contact with denatured dentin. Carious dentin excavation before SDF application is not necessary. As excavation may reduce the proportion of arrested caries lesions that become black, it may be considered for esthetic purposes. No rotary instruments will be used for caries removal.

The study participants will be allocated into one of the three parallel arms who will receive 38% SDF application as follows:
Study arm 1: annually (once a year; baseline visit);Study arm 2: bi-annually (twice a year at 6-month intervals; baseline visit and after 6 months);Study arm 3: four times a year (baseline visit, 2nd, 4th, and 8th week).

In the baseline visit in all the study arms, the child will be assessed for cavitated caries lesions and caries risk (ADA Caries Risk Assessment Form (Age 0–6)). After obtaining consent for the trial, SDF is applied on the selected caries teeth depending on the study arm. The demographic characteristics, plaque index, and caries status will be assessed. In the subsequent visits depending on the study arm, SDF will be applied (Table 1).

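### The six-month cut-off for analysing drop-outs and non-compliant children conflicts with the intention-to-treat definition, and it bears most on arm 3, the only arm with repeat applications before month 6

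*Protocol article*

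**What the plan says.** Five parts of the protocol article bear on who is analysed.

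- **Section 2.14 (Adverse Events)** lists allergy, taste and staining, then provides that if the child or parent "refuses to participate at any point in time owing to any of the above-mentioned conditions, he/she will be considered as a drop-out".
- **Section 2.13 (Compliance)** states: "If the child misses two rescheduled appointment, then it is referred to as non-compliant and the child is withdrawn from the study". It makes one exception, "if the child completes six months (1st outcome assessment) and then becomes non-compliant", in which case the child's time in the trial is used in the analysis.
- **Section 5 (Analysis Population and Missing Data)** states: "Dropouts (after six months) will be included in the analysis and values will be imputed for missing data". It also plans a sensitivity analysis on missing data and a report of withdrawal reasons by group.
- **Section 4 (Statistical Methods)** defines the intention-to-treat set as "considering all patients as randomized regardless of whether they received the randomized treatment". Superiority of four applications is accepted "only if shown to be superior using both the" intention-to-treat and per-protocol sets.
- **Section 2.12 (Study Implementation)** commits the site to try to follow each enrolled or randomised child for all 12 months.

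The schedules are in section 2.7 and Table 1. Arm 3 is treated "four times a year (baseline visit, 2nd, 4th, and 8th week"), arm 2 "bi-annually (twice a year at 6-month intervals; baseline visit and after 6 months"), and arm 1 at baseline only. Outcomes are assessed at 6 and 12 months in all arms.

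**The concern.** The exception in section 2.13 and the six-month qualifier in section 5 have a purpose only if earlier drop-outs and withdrawals are left out. An intention-to-treat set built that way is not the one section 4 defines. It holds children who stayed to month 6, and staying can depend on the allocated schedule.

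Arm 3 is the arm for which superiority is hypothesised. It is also the arm that asks families to come back for treatment three times before the cut-off. If early arm 3 losses are missing from both analysis sets, the intention-to-treat set no longer gives the independent check that the two-set rule in section 4 relies on.

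**Working it through.** The plan states no figure on this point, so there is none to reproduce. The check has a textual part and an illustration.

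**Step 1. The rules side by side.**

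| Situation | Sections 2.13, 2.14 and 5 | Section 4, intention-to-treat |
|---|---|---|
| Leaves or becomes non-compliant before the six-month assessment | Drop-out or withdrawn; not among those said to be analysed | Included as randomised |
| Leaves or becomes non-compliant after it | Included, by imputation or person-time | Included as randomised |

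The two columns differ in the first row only.

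**Step 2. Repeat applications and the cut-off (section 2.7, Table 1).**

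| Arm | Repeats before month 6 | Repeats at month 6 |
|---|---|---|
| 1 | 0 | 0 |
| 2 | 0 | 1, at the visit of the first outcome assessment |
| 3 | 3 (weeks 2, 4 and 8) | 0 |

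**Step 3. Possible loss in arm 3.** Input from section 2.11: 160 children per arm. Assumed, because the documents give no rate: a constant refusal rate r at each repeat, with each refusal ending participation. Share lost before month 6: q = 1 − (1 − r)³.

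- r = 2%: q = 1 − 0.98³ = 0.0588; × 160 = 9.4 children
- r = 5%: q = 1 − 0.95³ = 0.1426; × 160 = 22.8 children
- r = 10%: q = 1 − 0.90³ = 0.2710; × 160 = 43.4 children

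At the same rates, arm 2 would have 160 × r = 3.2, 8 or 16 refusals, all at the month-6 visit. Those children keep a first outcome if they attend it.

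**Step 4. Effect on the arm 3 estimate.** Let g be the arrest proportion in children kept minus that in children lost. The whole-arm proportion is (proportion in those kept) − q × g, so analysing only those kept shifts the arm 3 estimate by q × g. The sign is that of g.

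| Share lost q | g = 0 | g = ±10 points | g = ±30 points |
|---|---|---|---|
| 0.0588 | 0 | ±0.6 | ±1.8 |
| 0.1426 | 0 | ±1.4 | ±4.3 |
| 0.2710 | 0 | ±2.7 | ±8.1 |

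For scale, section 2.11 expects a difference of at most 14 points. The values of g are assumptions. The bias in a comparison between arms is the difference of the two arms' q × g, so similar early loss in the other arm would offset part of it.

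**The case against.** The strongest case against has five parts.

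1. *Section 2.14 speaks of refusing to participate.* A reader might infer that a child who attends but declines one application is dropped. The text does not say so, and calling a family that leaves the trial a drop-out is ordinary labelling. This stands. The conflict lies mainly in sections 2.13 and 5. Even so, an arm 3 family that stays away from reapplication visits, and misses the rescheduled ones, is withdrawn under section 2.13.
2. *Exclusion of early drop-outs is never stated outright.* Section 5 says who is included, not who is excluded, and it plans a sensitivity analysis. This also stands: the exclusion is implied. But it is the natural reading of sections 2.13 and 5 together, and an unspecified sensitivity analysis does not put these children back into the main analysis.
3. *Early loss is not confined to arm 3.* A reader might infer that refusals are lost in arm 3, kept in arm 2 and absent in arm 1. The documents do not support so clean a contrast. Every arm is treated at baseline and can lose families afterwards, and an arm 2 family that skips the month-6 visit has no outcome either. Table 1 also does not split the week 2, 4 and 8 examinations by arm, although section 2.10 says that the number of visits depends on the arm. What remains is that only arm 3 has repeat applications before the cut-off.
4. *Direction and size are assumed.* A reader might infer a bias towards arm 3 and an inflated false-positive rate. With 70% arrest assumed in children kept, one lesion per child and no other loss, the chance of wrongly finding arm 3 better than arm 1 could reach about 29%, against a nominal 2.5%. That figure also needs 10% refusal per repeat and a 30-point gap against the children lost. Nothing in the documents links taste, staining or allergy to lesion arrest, and parents have chosen SDF and been told of these effects. It is an extreme scenario, not an expected value.
5. *Section 5 also chooses between the per-protocol and intention-to-treat analyses by a 15% attrition limit.* This leaves open whether the two-set check in section 4 operates at all. It does not resolve the conflict over who belongs in the intention-to-treat set.

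**Conclusion.** The concern holds as a conflict between stated rules. Followed as written, sections 2.13 and 5, with the label in section 2.14, leave out children lost before the six-month assessment. That contradicts the intention-to-treat definition in section 4 and sits badly with the follow-up commitment in section 2.12. Arm 3 has more occasions for treatment-related or missed-visit withdrawal before the cut-off, with 3 early repeat applications against 0 and 0.

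The size cannot be fixed from the documents. A loss of about 9 to 43 of 160 arm 3 children rests on an assumed 2% to 10% refusal per repeat. The bias can go in either direction and is zero if those lost and those kept have the same arrest proportion. The wording should be corrected. Confidence is medium, because the exclusion is implied and the refusal rates are unknown.

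**What to change.** **Sections 2.13 and 2.14.** Treat a missed or refused application as stopping treatment only. Keep the child in the allocated arm and examine at 6 and 12 months, unless the parent withdraws from follow-up. Record the date, the reason and which application was refused.

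**Section 5.** Delete the words in brackets that restrict inclusion to drop-outs after six months. State that the intention-to-treat set holds all randomised children, with the same missing-data handling in every arm. Add a sensitivity analysis that counts early missing outcomes as not arrested. Leave these children out of the per-protocol set only.

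**Cost.** The change needs wording in three sections and effort to examine children who stop treatment, which may be hard in this population but which section 2.12 already promises. A true benefit may be diluted. If children who stop respond like the comparison arm, 14 points becomes 14 × (1 − q) = 13.2, 12.0 or 10.2 at 2%, 5% or 10% refusal per repeat.

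**Limit.** The protection depends on the children actually being examined. A child never seen after baseline has no outcome to build on, and imputing from children who stayed in the same arm can carry much of the same bias. Follow-up therefore matters more than the choice of imputation method.
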